  1. INTERVENTION

In addition to filling out the survey questions at four points in time (intervention 1), all participants will receive PRO feedback as a potential nudge (intervention 2). The PRO feedback will be a pdf report sent via email and available in their study participant profile, which graphically (line charts) shows the patients’ individual generic and disease-specific health status in comparison to the individual peer group. In addition to the visual feedback, the results will shortly be explained on the same page. The description will cover whether patient-individual PRO scores are better or worse compared to the peer group, and for longitudinal values, whether patient-related changes improved or worsened. Additional details on the scores, sub-scores, and calculations are shared with the patients on the following pages of the report. Peer groups are classified according to their disease, gender, and age group. The peer group is created based on individuals who have replied to the previous survey and will only be displayed if the group consists of at least four individuals. This threshold is set by the German General Data Protection Regulation. The report refers to the patients’ physicians as the main contact to discuss the results or in case of questions.

- 1. SAMPLE SIZE

The sample is drawn stratified randomly from insured patients of one large German statutory health insurance with about 9 million insured persons (of about 73 million statutorily insured persons in total in Germany) according to their diagnosis and/or disease management program status. A one-to-one matching of participants of one DMP with non-participants of a DMP but with the same proven diagnosis according to the ICD-10-GM system is made. Further stratification criteria are age group, gender, and health system utilization.

An initial invitation letter is sent to 200,000 insured individuals, 50,000 of each of the selected chronic conditions (about 25,000 per sub-cohort). Diabetes type 1 and type 2 are considered jointly as there is no differentiation in the selected PROMs. The patients of all chronic diseases are allocated to groups based on their participation in DMP (DMP or non-DMP group). Prior experiences suggest that around 30% of patients react to invitations to participate in research by their insurer [29-31]. Two-thirds of initial participants are expected to allow follow-up contacts and around 40% of these patients will continue participating in all the follow-up surveys after receiving reminders for each task. Therefore, after accounting for non-participants and participants with no complete survey data we expect a complete data set for 16,000 participants. However, the first research question will investigate response rates as there is no evidence on this population yet.

- 1. STUDY PROCEDURE

Eligible participants will be participating in the study for a maximum of four quarters, starting with the first access of the digital questionnaires followed by quarterly digital surveys split into several tasks. To start the survey, participants register with their study pseudonyms and share personal information, e.g., basic demographics and identification data. Each survey period contains four tasks to be completed by participants defined as sets of questions that each will take five to ten minutes to complete. The participants are invited to answer PROM and PREM surveys.
[figure not shown]

*Figure 1: Study design: Participants’ timeline and tasks*

As shown in Figure 1, the first point of contact will be a letter from the insurance to insured individuals with chronic diseases, who can then sign into the digital study via a QR code or link. For each of the different disease areas, a distinct care path is opened, with a sign-in process followed by selected PROMs and PREMs. The study covers a timeframe of one year with four overarching time intervals with dedicated questions. These are split into smaller tasks to facilitate the answering process for participants. The time intervals are split into smaller tasks to facilitate the answering process for participants. A few weeks after responding to the first set of questions (A & B), patients will receive a report with their individual PROM scores compared to a peer group, the PRO feedback (C). From the second interval onwards, patients will also receive the PRO feedback in a longitudinal visualization. Lastly, following the PRO feedback participants will be surveyed regarding their health behavior (D).

Figure 2 presents the questionnaires that will be used in the study per chronic disease group. PROM surveys include generic as well as disease-specific PROMs. The participants will receive individual reports on their patient-specific and peer group outcomes (PRO feedback) and will be asked about the comprehensibility of the report. Following the report, the participants receive a set of questions regarding the report’s comprehensibility and their health-related behavior.

[figure not shown]

*Figure 2: Survey items in the PROMchronic trial*

The primary data collected in this study is hence:

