  1. STUDY POPULATION

Inclusion criteria:

- Patient is at least 18 years old
- At least two outpatient consultations documenting a confirmed chronic disease diagnosis in 2021
- For type 1 diabetes at least one insulin prescription must be present in 2021

Exclusion criteria:

- Participation in more than one DMP

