**Secondary Outcomes**

Value of care:

Value of care delivery is assessed according to the Porter value-based healthcare framework:

Patient-Value = Outcome/Costs

In the analysis, we will firstly focus on the outcome side of the value equation and assess the outcome side based on PROMs and PREMs. The categorization into suspected high-value and suspected low-value care is hence based on PROMs and PREMs. Outcomes higher than average in at least two survey periods are classified as suspected high-value care whereas outcomes lower than average in at least two survey periods are classified as suspected low-value care. Outcomes not included in one of the categories will be separated and excluded from analysis (see Figure 4).

[figure not shown]

*Figure 4: Assessment of Value-Based Healthcare - Outcome dimension*

|  | **PROM – outcome (health)** | **PREM – outcome (responsiveness)** |
| --- | --- | --- |
| **Suspected low-value care** | Maximum one standard deviations above average in at least two survey periods | Maximum one standard deviations above average in at least two survey periods |
| **Suspected high-value care** | Maximum one standard deviations below average in at least two survey periods | Maximum one standard deviations below average in at least two survey periods |
| **Measure-ment** | Separately for health-related quality of life (PROPr index score) & disease-specific health (index score of the disease-specific PROM):   - COPD-related health status - Asthma-related health status - Coronary artery disease-related health status - Diabetes-related health status (for both types) | German responsiveness questionnaire index score |

*Table 1: Assessment of Value-Based Healthcare - Outcome dimensions and measurement*

To cover the cost-side of the value equation as well, we add the health care system utilization. For each of the chronic diseases average treatment costs will be calculated. Costs will cover all healthcare related costs (see 2.6 secondary data). Depending on the deviation from the average participants are classified in the following categories:

- Low costs: More than one standard deviation below average in at least two survey periods
- High costs: More than one standard deviation above average in at least two survey periods
- Inconspicuous costs: Else

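### A shared questionnaire is the only reason given for pooling type 1 and type 2 diabetes; it does not justify a shared reference group, so the smaller type's feedback, value and cost labels are confounded by diabetes type to an unknown degree

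*Protocol*

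**What the plan says.** Section 2.1 counts diabetes, types 1 and 2 together, as one of four disease areas. Section 2.5 gives the reason: "Diabetes type 1 and type 2 are considered jointly as there is no differentiation in the selected PROMs". No other reason appears.

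Three later comparisons depend on how the diabetes group is formed:

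- **Feedback (section 2.4).** The report tells each patient whether their scores are better or worse than those of a peer group. "Peer groups are classified according to their disease, gender, and age group". Diabetes type is not named.
- **Disease-specific PROM (section 5.2, Table 1).** The measurement row lists one diabetes-related health status covering both types.
- **Costs (section 5.2).** "For each of the chronic diseases average treatment costs will be calculated". All healthcare costs count, including the prescription costs listed in section 2.6. High or low cost means more than one standard deviation from the average in at least two survey periods.

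Elsewhere the protocol does separate the types. Section 2.2 codes them E10 and E11 for the non-DMP sub-cohorts, and section 2.3 sets a rule for one type only: "For type 1 diabetes at least one insulin prescription must be present in 2021".

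**The concern.** A common questionnaire means that both types can be scored on the same scale. It does not mean that their scores share a mean and spread, which is what a reference group requires. For costs the stated reason does not apply at all, since no PROM measures them. The eligibility rule also makes one cost component differ by design: every type 1 patient has an insulin prescription in 2021, whereas a type 2 patient need not have one.

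If the types differ on a score or on cost, a pooled average places patients of the smaller type partly according to their type. The third research question asks how patients react on learning that they do worse than a comparable group, so the comparability of that group is part of the question. For the second research question, differences in value-of-care labels between subgroups could reflect a different mix of types.

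**Working it through.** **The protocol's own figure.** Section 2.5 expects 16,000 complete data sets. 200,000 x 0.30 = 60,000; x 2/3 = 40,000; x 0.40 = 16,000. It reproduces, and pooling does not affect it.

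**Size of the diabetes cohort.** The same rates applied to the 50,000 invited with diabetes give 15,000 first respondents, 10,000 allowing follow-up and 4,000 completers. The type 1 share f is not stated. At an assumed 5-20%, that is 750-3,000 type 1 first respondents and 200-800 completers.

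**Assumptions for the effect.** None of these is in the protocol: f = 5-20%; type 1 mean minus type 2 mean D = 0 to 1 within-type SD; normal scores with SD 1 within type; correlation between a patient's four periods 0.5-0.9.

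**Single score against the pooled mean.** The pooled mean, measured from the type 2 mean, is fD. The share of type 1 patients beyond it, on the side of the difference, is Phi((1 - f)D). At f = 0.1 and D = 0.5 this is Phi(0.45) = 67%, against 50% with a type-specific mean.

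**Label beyond one SD in at least two of four periods.** This is the rule as written for costs. The pooled SD is sqrt(1 + f(1 - f)D^2). At f = 0.1 and D = 0.5 it is sqrt(1.0225) = 1.011, so the upper limit is 0.05 + 1.011 = 1.061. Seen from the type 1 mean, that is 1.061 - 0.5 = 0.561 SD instead of 1 SD. Simulation with 400,000 patients over the assumed ranges gives:

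| D | Type 1 beyond pooled mean, single score | Type 1 high label | Type 1 low label |
| --- | --- | --- | --- |
| 0 | 50% | 17-18% | 17-18% |
| 0.2 | 56-58% | 22-24% | 12-14% |
| 0.5 | 66-68% | 29-35% | 6-9% |
| 1.0 | 79-83% | 43-57% | 2-3% |

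With a type-specific mean and SD, the high and low label rates stay at about 17-18% whatever D is. Type 2 moves little under pooling: at D = 0.5 its high-label rate is 13-17%.

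**Overall diabetes share.** At f = 0.1, D = 0.5 and correlation 0.7, the high-label rates are 32.9% for type 1 and 15.9% for type 2. Overall: 0.1 x 0.329 + 0.9 x 0.159 = 17.6%, the same as the type-specific rate of 17.6%.

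**Subgroup shares.** With the same rates, a subgroup with 20% type 1 shows 0.2 x 0.329 + 0.8 x 0.159 = 19.3%, and one with 5% shows 0.05 x 0.329 + 0.95 x 0.159 = 16.8%. That gap comes from type mix alone.

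**The case against.** **The difference between types is assumed.** This stands. No section says that the types differ on any score or on total cost, and the insulin rule is an eligibility criterion. A reader might infer that the labels show diabetes type instead of standing among comparable patients. The protocol does not support that: the labels would mix both, and the type part is nil at D = 0.

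**The pooling of peer groups and costs is inferred.** This also stands in part. The pooling sentence is in the sample-size section; sections 2.4 and 5.2 speak only of disease. Table 1's reference to both types is in its measurement row and may mean only a common instrument. Pooling is still the natural reading, because section 2.1 counts diabetes as one disease area and no section uses type for these comparisons. For the generic PROM and the PREM the reference group is not stated at all, so the point does not extend to them with the same force.

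**Peer groups are stratified by age group and gender.** True, and the type mix may vary between cells. The single-score figures describe one unstratified pool, so they do not estimate the planned feedback. Nor must type 1 be the minority in every cell. Section 5.2 sets no such strata for the value and cost averages.

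**Costs need not be normal.** Correct. The simulation shows how a one-SD rule responds to a shift; it does not estimate the planned cost label.

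**Later analyses could adjust.** Section 5.2 plans regressions on significant patient characteristics and other collected variables, and section 5.1 plans sensitivity analyses. Adjustment is therefore possible, although type is not named. It cannot undo a report already sent.

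**Type-specific references hide real differences between types.** This is a genuine cost, and a reason to keep the pooled version beside the new one.

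**Conclusion.** The point holds in a limited form. The stated reason supports a common questionnaire but not a common reference group, and it is irrelevant to costs. On the natural reading, the feedback, disease-specific value label and cost label of the smaller diabetes type are confounded by type to a degree that the protocol does not allow to be quantified. The 29-35% against 17-18% is an illustration at 0.5 SD on a normal scale.

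A reader might also infer that the share of high- or low-value care in diabetes as a whole is biased. The working does not bear this out: that share hardly moves. What is distorted is which patients carry the label, and so comparisons by type or between subgroups with a different type mix. Section 2.5 matches DMP and non-DMP patients on the same ICD-10-GM diagnosis. If that is done at the E10/E11 level, it limits the imbalance between those two groups at invitation, though not necessarily among respondents.

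The sample size and the primary representativeness outcome are unaffected.

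**What to change.** Keep one diabetes recruitment cohort and one questionnaire, and change the reference groups:

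- Compute the average and SD for the disease-specific PROM label and the cost label separately by diabetes type. Take type from the claims diagnosis or the DMP program type (section 2.6), and state a rule for patients who carry both codes. Section 2.2 defines E10 and E11 only for the non-DMP sub-cohorts, so the source for DMP participants must be stated too.
- Report the pooled version as a sensitivity analysis, so that any difference between the types stays visible.
- Where type can be passed to the survey platform, add it to the feedback peer group. If a cell has fewer than four respondents, the display minimum in section 2.4, merge neighbouring age groups within type. Where type cannot be passed on, say in the report that the peer group contains both types.

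The cost is one grouping variable, a rule for assigning it, some small type 1 cells and one extra analysis. Type must already be known at sampling to apply the insulin criterion. The protocol does not say whether the platform holds it, so the feedback part depends on that.

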- Using machine learning predictive models (long-short-term memory deep learning network for time trend classification, random forest, logistic regression, decision tree and/or support vector machine) to identify admission risk in Q3 and Q4 based on PROMs/PREMs in Q1 and Q2

*PRO feedback*

- Mainly: Statistically significant change in at least one of the health care behavior dimensions (see 4.2) and comparison of participants who opened the report vs. those who did not, using logistic regression (change/no change)
  - Physical activity: Shift of participants to a higher category
  - Nutrition: Shift of participants to “More healthy” from any other category
  - Tobacco: Shift of participants to a lower category
  - Alcohol: Shift of participants to a lower category
  - Sleep: Share of stable participants (no significant variation in sleep duration)
- Secondly: Descriptive exploratory analysis of the rates of the following two evaluation dimensions and statistically significant differences in subgroups (see 5.1 and 4.3):
  - Understandability
  - Helpfulness
  - Emotional change

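### As the protocol text stands, health behaviour is first asked after the first feedback report, so the nudge analysis has no pre-report value and answers its question only in part.

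*Protocol*

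**What the plan says.** Protocol 2.6 (Study Procedure) gives the order of tasks within a survey period. Sign-in comes first. At registration participants "share personal information, e.g., basic demographics and identification data", and the care path is described as "a sign-in process followed by selected PROMs and PREMs". The report follows: "A few weeks after responding to the first set of questions (A & B), patients will receive a report with their individual PROM scores". Behaviour comes last: "following the PRO feedback participants will be surveyed regarding their health behavior (D"). A later paragraph of the same section repeats the order: "Following the report, the participants receive a set of questions regarding the report’s comprehensibility and their health-related behavior".

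The list of primary data in 2.6 names five behaviour dimensions (activity, nutrition, tobacco, alcohol, sleep) but gives them no timing of their own. The demographic items contain none of them.

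Under PRO feedback, 5.2 makes the main outcome "Statistically significant change in at least one of the health care behavior dimensions". It is analysed by logistic regression on change versus no change, comparing those who opened the report with those who did not. For activity, tobacco and alcohol, change is a move to a better category. For nutrition it is a move to *More healthy*. Sleep is scored as stability. Section 2.4 (Intervention) sends the feedback to all participants.

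**The concern.** A category shift needs a starting value. In the order described, the earliest value any participant can supply is D of period 1 (D1), and the first report has been sent by then. If a participant reads report 1, becomes more active and then answers D1, the improvement sits in the starting value. If it lasts, every later comparison records no change.

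At stake is the sub-question in 1.2 on whether feedback acts as a positive nudge. The main analysis of that question would miss whatever the first report achieves quickly. A statistical analysis plan cannot repair this, because it cannot supply a measurement that was not taken.

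**Working it through.** **1. The order, set side by side**

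| Step in period 1 | Content named in 2.6 | Behaviour items named? |
|---|---|---|
| Registration | Demographics, identification data (given as examples) | No |
| A and B | PROMs and PREMs | No |
| C | First report | No |
| D (D1) | Report comprehensibility, health behaviour | Yes, first mention |

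**2. Could another part of the protocol supply the starting value?** The insurer data listed in 2.6 cover contacts, prescriptions, diagnoses and costs. They do not measure the five behaviours. Section 5.3 plans comparisons before and after the intervention for utilization only. Everyone is sent the report, so there is no unexposed group. Non-openers are self-selected, and without a pre-report value prior behaviour cannot be adjusted for.

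**3. How much is lost.** Let e be the true effect of report 1 on the probability of a favourable shift among openers, and f the share of e that occurs before D1. If later reports add nothing,

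visible difference after D1 = e × (1 − f).

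The value of f depends on the interval from C to D, which is not stated, so the loss ranges from 0% (f = 0) to 100% (f = 1).

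**4. Would the large sample help?** The protocol's completer figure in 2.5 reproduces: 200,000 × 0.30 × 2/3 × 0.40 = 16,000. The other inputs are assumptions for illustration: 70% open the report (11,200 versus 4,800), the background shift rate is p0 = 10%, and e = 5 points. The test is two-sided at 0.05.

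Power ≈ Φ[(d − 1.96 × SE0) / SE1], where d is the visible difference, SE0 the pooled and SE1 the unpooled standard error.

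For f = 0.5:
- d = 0.025, so the openers' rate is 0.125 and the pooled rate is 0.7 × 0.125 + 0.3 × 0.10 = 0.1175.
- SE0 = √[0.1175 × 0.8825 × (1/11,200 + 1/4,800)] = 0.00556.
- SE1 = √[0.125 × 0.875/11,200 + 0.10 × 0.90/4,800] = 0.00534.
- Power = Φ[(0.025 − 0.01089)/0.00534] = Φ(2.64) = 99.6%.

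| f | Visible difference | Power |
|---|---|---|
| 0 | 5.0 points | about 100% |
| 0.5 | 2.5 points | 99.6% |
| 1 | 0 points | 2.5% (chance rejection in one tail) |

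With this sample, a halved effect would still be detected but reported at half its size. An effect that is complete before D1 would not be seen at any sample size.

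**5. Later reports.** With four periods, three of the four reports fall between D1 and D4, and one of the first two falls between D1 and D2. If each report added the same effect, fully realised before its own D, 1/4 or 1/2 of the total would be missed. That full-realisation condition is an assumption, not something the protocol states.

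**The case against.** The strongest reply is that the prose is not a complete item map. Section 2.6 refers to Figure 1 for the timeline and Figure 2 for the items, and neither was available here. The registration content is given by example only, and nowhere does the text say that behaviour is asked in D alone. This stands as a limit on certainty. But the text states the order twice and names no earlier item, so figures that differ would contradict it and need reconciling.

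Several further points also stand:

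- **Not all of the report-1 effect is hidden.** A reader might infer that the first report's effect cannot be seen at all. That holds only for effects complete before D1. Slower changes enter the D1 to D2 comparison, mixed with report 2.
- **D1 is not post-exposure for everyone.** For a participant who did not open report 1, it is an unexposed value. For one who first opens a later report, the preceding D is a genuine pre-exposure value. The longitudinal display begins only with the second interval.
- **No sign reversal.** A reader might infer that a fading response would appear as net worsening among openers. The outcome in 5.2 is coded one way, so a relapse after D1 counts as no change. The planned analysis produces no negative quantity.
- **Not all dimensions are plain shifts.** Sleep is scored as stability, and *More healthy* may be a self-rated change. The items on triggers and plans for change may also capture self-attributed change. None of these supplies a starting value for activity, tobacco or alcohol.
- **A baseline would not make the contrast causal.** Opening the report remains self-selected.

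**Conclusion.** The point holds in limited form. As written, the first behaviour value follows the first report. For participants who opened that report, effects occurring before D1 are absorbed into the starting value and coded as no change. Non-openers have no such loss, so the contrast is biased, probably toward no effect. Between 0% and 100% of the report-1 effect is lost, depending on an interval the protocol does not give. Research question 3 is therefore answered in part, since later reports and delayed effects remain assessable.

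The conclusion assumes that the unseen figures agree with the text of 2.6. It does not support a claim that the nudge question is unanswerable or that the trial's main result is affected: the primary endpoint in 4.1 is representativeness. It should be fixed, but it does not threaten the study's principal aim.

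**What to change.** - In 2.6, add the five behaviour items to task A or B of period 1, before the report is released, and keep them in D. Check Figures 1 and 2 against the text and make them agree.
- In 5.2, define change from the pre-report value to D of a named period, and include the pre-report value as a covariate in the logistic regression.
- State the planned interval between C and D.
- If period 1 is already fielded, say in 5.2 that D1 is a post-report value and limit the claim to change after D1.

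The cost is protocol wording plus one extra administration per participant of five items that already exist, a small one-time addition to the survey burden. If fielding has begun, the cost is wording and a narrower claim.
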